### Primary outcome measures

The primary outcomes for social anxiety disorder will be reductions in measures of social anxiety disorder: the Social Phobia Scale and Social Interaction Anxiety scale [83]. The primary outcome measures for alcohol are a reduction in the number of standard drinks per drinking day, assessed using the TLFB [75,76] and in the Severity of Alcohol dependence Questionnaire (SADQc) [84]. Quality of Life will be assessed by the SF12 [85].

### Secondary outcome measures

Secondary outcome measures are: the number (proportion) of days abstinent during the past 90 days; two time to event measures: (i) time to first drink; (ii) time to first heavy drinking day “relapse”, defined as three consecutive days drinking ≥ 6 standard drinks for a man and ≥ 4 standard drinks in a day for women) assessed using the TLFB [75,76]; the Depression, Anxiety and Stress Scale scores [87], and Days out of role from the Brief Disability Questionnaire [88].

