All interviews will be audio-taped and a random sample of 25% will be rated by a PhD level Clinical Psychologist with relevant diagnostic experience, to determine diagnostic reliability. Measures used in the study are shown in Table 1 and include: the Anxiety Sensitivity Index [73]; Kushner’s Alcohol Outcome Expectancies Questionnaire [74]; the Timeline Follow-Back (TLFB) method for quantifying alcohol consumption over the previous 28 days [75,76]; the Opiate Treatment Index (OTI) to assess drug (and medication) quantity and frequency during the previous 28 days [69]; the Penn Craving Scale [77]; Self efficacy for abstinence [78]; the University of Rhode Island Change Assessment [79], used to assess motivation; Health Service Utilisation questions [80], used to asses other treatment received in study period.

**Table 1 T1:** Schedule of assessments

**Assessment**	**Telephone contact**	**Pre treatment**	**Post washout**	**Post treatment**	**3 month follow-up**	**6 month follow-up**
*Eligibility*						
Alcohol Use Disorders Identification Test (AUDIT) [64]	+	-	-	-	-	-
Mini Social Phobia Inventory (Mini-SPIN) [65]	+	-	-	-	-	-
Clinical Institute Withdrawal Assessment for Alcohol Revised (CIWA-AR) [70]	+	-	-	-	-	-
Suicide Behaviours Questionnaire-Revised (SBQ-R) [81]	+	-	-	-	-	-
Psychosis Screening Questionnaire [67]	+	-	-	-	-	-
Anxiety Disorders Interview Schedule for DSM-IV (ADIS-IV) [82] incorporating International Personality Disorders Examination Avoidant Personality Disorder questions (IPDE) [72]	-	+	-	-	+	-
*Primary outcome measures*						
Social Phobia Scale and Social Interaction Anxiety Scale (SPS/SIAS) [83]	-	+	+	+	+	+
Time Line Follow Back (TLFB) [76]	-	+	+	+	+	+
Severity of Alcohol Dependence Questionnaire (SADQc) [84]	-	+	+	+	+	+
General Health functioning SF12 [85].	-	+	-	+	+	+
Blood for LFTs, FBC, CDT, Electrolytes	-	+	-	-	+(1)	-
*Secondary outcome measures*						
Sheehan Disability Scale(SDS) [86]	-	+	-	+	+	+
Depression, Anxiety and Stress Scale (DASS-21) [87]	-	+	+	+	+	+
Days out of role from the Brief Disability Questionnaire [88]	-	+	-	+	+	+
Drinker Inventory of Consequences (DRINC) [89]	-	+	-	+	+	+
*Static and varying covariates*						
Family Tree Questionnaire (FTQ)		+				
Anxiety Reduction Subscale of the Alcohol Expectancies Questionnaire [90]	-	+	-	+	+	+
Kushner’s Alcohol Outcome Expectancies Questionnaire [74]	-	+	-	+	+	+
Penn Alcohol Craving Scale(PACS) [77]	-	+	-	+	+	+
Alcohol Abstinence Self Efficacy Scale (AASES) [78]	-	+	-	+	+	+

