### Analyses

Random effects regression models will be used to compare the efficacy of the treatment conditions on outcome measures from an intention to treat perspective. Random effect regression models (also known as hierarchical linear or mixed models) have been used in clinical trials involving relapse, and are suited to repeated measures, missing observations, and longitudinal data [99]. Random effects regressions can also account for variance associated with the clustering found with group treatment and multiple treatment sites. Cox regression will be used to determine time from baseline to first drink, time to first heavy drink. Last-point carried forward or multiple imputation will be used to determine the scores of participants who drop-out and are not located at follow-up.

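### The only TLFB window the article states is 28 days, which cannot supply the secondary 90-day abstinence outcome or a continuous calendar for the two event times

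*Protocol article*

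**What the plan says.** Three sections of the protocol article bear on this.

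- **Assessment.** The list of study measures includes "the Timeline Follow-Back (TLFB) method for quantifying alcohol consumption over the previous 28 days". The list is introduced as the measures used in the study and refers to Table 1, so it is not confined to baseline. Table 1 schedules the TLFB at pre-treatment, post-washout, post-treatment, 3 months and 6 months, with no separate window for any visit.
- **Secondary outcome measures.** The outcomes include "the number (proportion) of days abstinent during the past 90 days" and "two time to event measures: (i) time to first drink; (ii) time to first heavy drinking day". The second event is labelled relapse and defined by three consecutive days at or above a drinking threshold. The TLFB is named as the instrument.
- **Analyses.** "Cox regression will be used to determine time from baseline to first drink, time to first heavy drink".

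On timing, the Follow-up section places assessments at the end of treatment and three and six months later. Under Treatment and treatment sites, participants also keep daily diaries that record drinks. The diaries are described as part of treatment, do not appear in Table 1 and are not named as a source for any outcome.

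**The concern.** A count over 90 days needs 90 days of data, and the instrument as described returns 28. Time to first drink needs a day-by-day record without breaks from the time origin, and a relapse defined by consecutive days needs the same. If each interview looks back only 28 days and interviews are about 90 days apart, most of each follow-up interval falls outside every interview.

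Two things would follow. The abstinence proportion at 3 and 6 months would have no data for most of its denominator. In the Cox models, a participant whose first drink fell in a gap would be given a later event date, or would be counted event-free if the drinking did not recur inside a window. Recall not collected at the visit cannot be reliably recovered afterwards, so this has to be settled before the interviews are held.

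**Working it through.** The document gives no coverage figure to reproduce. The check is day-counting.

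**Inputs from the article**
- TLFB window: 28 days (Assessment).
- Abstinence window: 90 days (Secondary outcome measures).
- Event-time origin: baseline (Analyses).
- TLFB visits after baseline: post-washout, post-treatment, 3 months, 6 months (Table 1).
- Washout: one month, with randomisation after it (Procedure).
- Treatment: nine weekly sessions, to be finished within five months of initial assessment (Procedure).

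**Assumed conversions**
- Washout 28-30 days.
- Three-month gaps 90-91 days.
- Treatment from 9 × 7 = 63 days up to 152 − 28 = 124 days, taking five months as about 152 days.

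**1. 90-day abstinence at the 3- and 6-month visits**
- Covered: 28/90 = 31.1%.
- Uncovered: (90 − 28)/90 = 62/90 = 68.9%.
- The preceding TLFB took place about 90 days before, so it contributes nothing to this window.

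**2. 90-day abstinence at post-treatment, if it is reported there**
- With 63 days of treatment, the post-washout TLFB supplies another 90 − 63 = 27 days. Uncovered: (90 − 28 − 27)/90 = 35/90 = 38.9%.
- With treatment of 90 days or more, the uncovered share is again 68.9%.
- In the 63-day case, the same 27 of 90 days (30%) precede randomisation and lie in the washout month.

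**3. Event times, TLFB alone, baseline to the 6-month visit**
- Uncovered share = 1 − (4 × 28)/(washout + treatment + two follow-up gaps).
- Shortest schedule: 28 + 63 + 180 = 271 days; 1 − 112/271 = 58.7%.
- Longest schedule: 28 + 124 + 182 = 334 days; 1 − 112/334 = 66.5%.
- Range: about 59-67%.

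**4. Event times if the diaries filled every day to the end of treatment**
- Uncovered share = 2 × (gap − 28)/total days.
- Highest: 2 × 63/(28 + 63 + 182) = 126/273 = 46.2%.
- Lowest: 2 × 62/(28 + 124 + 180) = 124/332 = 37.3%.
- All of this lies in the two follow-up intervals, where about 69% of days stay uncovered.

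**The case against.** The best defence is that 28 days is one descriptive phrase, placed after the account of the initial assessment, while 90 days matches the spacing of the follow-up visits. A fuller protocol may state a longer recall at follow-up. That is possible, and if so the correction is only to the wording. But the article gives two numbers for what must be the same record, and the 28-day phrase applies to the measures used across the study. This is a conflict between stated rules, not a detail left out of a condensed article.

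A second defence is grammatical. The reference to the TLFB follows the event-time items, and the abstinence item is set off by a semicolon. However, no other instrument is offered for daily drinking. The Opiate Treatment Index, which covers drugs and medication, also looks back 28 days.

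Four stronger readings may tempt a reader, and the document does not support them.

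- **That about two thirds of the needed days are never observed.** Diaries record drinks during treatment, and the post-washout TLFB covers nearly all of the washout. The 69% figure belongs to the 90-day window at 3 and 6 months.
- **That event-time coverage should be counted from randomisation.** The Analyses section says baseline, which brings a fourth TLFB window into the count.
- **That washout days contaminate the abstinence outcome.** This arises only if 90-day abstinence is used at the post-treatment visit, which the article does not say. Both arms have the same washout.
- **That Hypothesis 2 rests on these outcomes.** Sustained lower consumption can also be tested on the repeated primary drinking measures with the planned random effects models.

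The objection is also right that only secondary outcomes are touched and that the visit schedule is the same in both arms. No direction of bias between arms has been shown. The diaries are still not a ready substitute: they are not assigned this role and are not described for follow-up.

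**Conclusion.** The inconsistency is real and confined to secondary outcomes. As written, 90-day abstinence cannot be computed at the 3- and 6-month visits, because 62 of 90 days (69%) before each are uncovered. For time to first drink and time to relapse, about 59-67% of days from baseline to the 6-month visit fall outside the TLFB, or about 37-46% if complete treatment diaries were brought in. Events in those gaps would be missed or misdated.

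The 69% depends only on the two stated windows and the three-month spacing. The event-time ranges also depend on the assumed conversions of months to days and on treatment lasting between 63 and about 124 days. Drinks per drinking day can be computed from 28 days and is not affected. The sample size plays no part in this point.

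**What to change.** Reconcile the Assessment, Secondary outcome measures and Analyses sections as follows.

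- State that the TLFB at post-treatment, 3 months and 6 months covers every day since the previous assessment, and at least 90 days at the 3- and 6-month visits. Coverage of the 90-day window then rises from 28/90 to 90/90 at those visits.
- Build both event times from that continuous calendar.
- Take the 28-day primary drinking measure as a subset of the same record.
- If 90-day abstinence is also reported at post-treatment, restrict it to post-randomisation days so that the prescribed washout month is not counted.

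If a longer follow-up recall was intended all along, correcting the Assessment wording is enough for the first item. Redefining abstinence over the past 28 days would match the stated instrument, but it would not supply the event times.

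The cost is a longer interview at visits already scheduled and somewhat weaker recall of older days. This is greatest at post-treatment for slow completers, where recall could reach about 124 days. No new visits are needed.

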### Procedure

After baseline assessment, all participants will complete a pre-treatment session of motivational interviewing followed by a 1 month “washout” period of abstinence. Symptoms of social anxiety (SPS and SIAS), general anxiety and depression (DASS) will then be reassessed. After reading and signing a written information and consent form, participants will be individually randomised by the sealed envelope method to one of two treatment conditions, of either: i) Treatment for alcohol use disorder comprising 9 weekly sessions of individual CBT for alcohol use disorder; OR ii) Treatment for alcohol use disorder and social anxiety disorder comprising 9 weekly sessions of integrated individual CBT for alcohol use disorder and anxiety disorder.

Each therapy session will last 60 to 90 minutes and will be conducted by one therapist (Clinical Psychologist). Both treatment conditions will have the same therapists and equal exposure to face-to-face treatment, approximately 10–15 hours, over a total of approximately three to five months.

Participants will be encouraged to attend treatment sessions weekly where possible, but will be given a maximum time frame of 5 months from initial assessment in which to complete treatment. Post and follow up assessment time points will be calculated from the end of all treatment sessions (1 motivational interviewing session plus 9 treatment sessions).

Participants will be considered non-completers if they miss more than 2 treatment sessions, or if they fail to complete the course of treatment within five months from assessment. Therapists will make at least 3 attempts to reschedule missed appointments, followed by a handwritten note two weeks after the last phone contact to i) acknowledge client’s decision to leave treatment, ii) encourage return to treatment, and iii) provide information about how this can be achieved. Participants who nevertheless choose to discontinue treatment will be contacted for post and follow up assessments calculated as if treatment were completed 3 months from the initial assessment.

### Treatment and treatment sites

Treatment will be provided at the Emotional Health Clinic, Centre for Emotional Health, Macquarie University, or Drug Health Services at Royal Prince Alfred Hospital (Sydney South West Area Health Service) and comprise one pre-treatment session followed by 9 weekly sessions. Two additional supplementary sessions can be used at treating therapist discretion to deal with crises that may emerge. The therapeutic approach will integrate CBT skills with a motivational interviewing style. Participants will complete monitoring diaries daily (recording the number of drinks consumed and rating their mood, anxiety and craving for alcohol), read educational material and complete take home tasks. The treatment goal is short-term abstinence (≥3 months), with participants selecting individual goals within recommended drinking guidelines beyond that period.

After an initial “washout” period of abstinence (≥ 1 month), goals for alcohol reduction will be determined collaboratively. Thus, participants may select a goal of abstinence, or controlled use within recommended drinking guidelines. Offering a choice of treatment goals will facilitate the inclusion of participants with various levels of dependence and decrease the risk of early drop-out [93].

### Participant retention

Participant retention will be maximised through a range of methods. Participants will be asked to provide at least two alternative contacts (e.g., Family member, partner or professional with whom they have regular contact) in addition to their own phone number and address, and if applicable email address. Regular contact (including study information letters, birthday cards and appointment reminder messages) with participants prior to, during and after their treatment will be maintained up until the final assessment at 6 months post treatment. During this time alternatives for data collection may be employed where they are in line with study protocol (e.g., conducting interviews by phone or email, or conducting sessions at sites more convenient for participants – e.g., home visits). Participants will be reimbursed $25 for their time attending follow-up assessments.

### Pre-treatment session

The aim of the pre-treatment session of motivation enhancement therapy is to place an unequivocal focus on the importance of addressing drinking and commit to an initial “washout” period of abstinence (≥ 1 month). There is little evidence that without substantial changes to substance use patterns treatment for anxiety disorders can be successful. This session is also designed to engage the individual in the treatment process at this crucial stage. In this session, which is based on the work of Miller et al. [94,95], the goal is to provide personalised feedback of the assessment of alcohol-related difficulties, check participants’ progress and increase or consolidate their commitment to reduced drinking and treatment in general; the session will also orient the person to the treatment program and introduce daily monitoring. A consultation with a medical practitioner will be organised to assess suitability for pharmacotherapy with naltrexone (50 mg daily). Participants will be reimbursed for costs associated naltrexone should it be prescribed.

### Treatment for alcohol use problems only

The components of this widely used CBT intervention include [96,97]: orientation to treatment approach; assessing high risk situations; coping with cravings and urges; managing thoughts about alcohol and drinking; problem solving; drink refusal skills; planning for emergencies; seemingly irrelevant decisions; dealing with a lapse and relapse prevention.

### Combined integrated treatment for alcohol use problems and social anxiety disorder

Based on the work of [name] [47,51], Monti et al. [97] and our own review of the literature [62], we have developed an integrated cognitive behavioural treatment for comorbid social phobia and alcohol use disorders [63]. The intervention is based on a unified model of the interplay between social anxiety disorder and drinking. Initial sessions provide information about drinking and social anxiety disorder and their interaction, encourage awareness of individual triggers for drinking and anxiety through reflection on diaries and begin graded exposure and behavioural experiments within session as well as teaching techniques for challenging unhelpful thoughts, refusing drinks, and managing anxiety and cravings. Focusing on successes achieved during sessions helps to maintain motivation. Subsequent sessions extend graded exposure to more advanced behavioural experiments to progressively build coping skills. Each session involves techniques to build self-efficacy and self-mastery over anxiety and drinking. Detailed participant and therapist manuals have been developed and will be available from the authors at the completion of the trial.

Clinical supervision of the treating therapists will be provided for 1 hour per day with the 1^st^ or 2^nd^ author in order to assure the quality and fidelity of the interventions. Both [name] & CS are experienced clinical psychologists with additional training and experience in clinical supervision.

### Safety net

Participants who show deterioration in functioning requiring residential or psychiatric treatment will be referred to the appropriate specialist treatment services (anxiety clinics, psychiatric services or alcohol and other drug services). They will remain in the study but their outcome will be designated as relapsed (for anxiety, alcohol or both as appropriate). Either the last point carried forward or multiple imputation will be used to estimate possible scores so as to include these participants in analyses.

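### Scores of participants referred for deterioration are to be estimated although they stay in the study, with no limit to missed assessments and no link to the defined outcomes

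*Protocol article*

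**What the plan says.** The rule is in the Safety net section of the protocol article. Its trigger is clinical: "Participants who show deterioration in functioning requiring residential or psychiatric treatment will be referred to the appropriate specialist treatment services". Two statements about outcome data follow. The first is a label: "They will remain in the study but their outcome will be designated as relapsed (for anxiety, alcohol or both as appropriate". The second is a scoring rule: "Either the last point carried forward or multiple imputation will be used to estimate possible scores so as to include these participants in analyses".

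Other sections bear on the same people:

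- **Analyses** names the same two methods, but only for participants who drop out and cannot be found for follow-up. The main analysis is a random effects regression by intention to treat.
- **Procedure** keeps even those who stop treatment in follow-up: "Participants who nevertheless choose to discontinue treatment will be contacted for post and follow up assessments".
- **Participant retention** allows data collection by phone or email and allows home visits.
- **Follow-up** provides reassessment by a blinded research assistant at end of treatment, three months and six months. It makes no exception for referred participants.
- **Primary outcome measures** are scale scores or quantities. For anxiety: "The primary outcomes for social anxiety disorder will be reductions in measures of social anxiety disorder: the Social Phobia Scale and Social Interaction Anxiety scale". For alcohol they are drinks per drinking day and the SADQc, and for quality of life the SF12.
- **Secondary outcome measures** define alcohol relapse by a drinking pattern on the Timeline Follow-Back (TLFB): "ii) time to first heavy drinking day “relapse”, defined as three consecutive days drinking ≥ 6 standard drinks for a man", with a lower threshold for women.

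**The concern.** The scoring rule depends on having been referred, not on a score being absent. Read literally, it applies estimation to people who remain available for measurement. The trial would then have two rules of different scope for overlapping groups, one in Safety net and one in Analyses.

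The label and the score can also disagree. The same participant may be called relapsed and carry an estimated score that shows no worsening. The section does not say which of the two enters which analysis.

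At stake is the between-arm comparison on the continuous primary outcomes. If more participants deteriorate in one arm, and their estimated scores are better than their true ones, that arm is flattered. The relapse analysis is unclear too, because a referral is not the event that the listed time-to-relapse outcome counts. Only the coding of outcomes is questioned here, not the referral of participants to care.

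**Working it through.** The plan gives no figure for this rule, so there is none to reproduce. The check sets the sections side by side and then illustrates the size.

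**1. Scope of estimation.** Safety net: everyone referred for deterioration, all remaining in the study. Analyses: only drop-outs who are not found. A referred participant who attends the three-month visit falls under the first rule and not the second. Procedure, Participant retention and Follow-up provide the means to obtain that participant's blinded score.

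**2. Which value would be carried forward.** Under Procedure, the one-month abstinence washout precedes randomisation and treatment. Table 1 schedules SPS/SIAS, TLFB and SADQc post washout and next at post treatment. For someone who deteriorates during treatment, the last available value on these measures is therefore normally the post-washout one. The TLFB covers the previous 28 days, so if the washout was kept it records about a month of abstinence, close to the best possible drinking record. For SPS and SIAS the post-washout value is simply one that predates the deterioration. The SF12 is not scheduled post washout, so its last value would be the pre-treatment one.

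**3. Match between label and outcomes.**

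| Label | Trigger in Safety net | Nearest listed outcome | Match |
|---|---|---|---|
| Relapsed, anxiety | Referral | SPS and SIAS reductions | None; no anxiety relapse is listed |
| Relapsed, alcohol | Referral | Time to relapse on TLFB drinking days | Different trigger; no event date given |

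**4. Size.** Let p1 and p2 be the shares deteriorating in the two arms, and g the gap in SD between the true and the estimated score. Estimation shifts each arm mean by p × g, so

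bias in the arm difference ≈ (p1 − p2) × g.

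The documents give neither the shares nor the gap; all values below are assumptions. The planned effect of 0.5 comes from Determination of sample size. With g = 1 SD:

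| Assumed shares | Bias (SD) | Share of 0.5 |
|---|---|---|
| equal | 0 | 0% |
| 2% vs 1% | (0.02 − 0.01) × 1 = 0.01 | 2% |
| 10% vs 5% | (0.10 − 0.05) × 1 = 0.05 | 10% |
| 15% vs 5% | (0.15 − 0.05) × 1 = 0.10 | 20% |

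The sign depends on the arm. Take shares of 10% and 2% and g from 0.5 to 1.5 SD, which gives a bias of 0.08 × 0.5 = 0.04 to 0.08 × 1.5 = 0.12. A true effect of 0.50 then appears as 0.46 to 0.38 if the alcohol-alone arm has more deterioration, and as 0.54 to 0.62 if the combined arm has more.

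**5. Multiple imputation.** The direction depends on the imputation model and on whether the deterioration is used in it. A model that ignores the deterioration would tend to be optimistic, but no fixed direction follows.

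**The case against.** The strongest defence is that Safety net is only a missing-score rule. Estimating scores so that people can be included in analyses is naturally read as covering scores that would otherwise be absent, and the follow-up provisions elsewhere support that reading. This stands in part. A reader might infer that observed scores are discarded and the worst outcomes replaced by better ones, but the text does not say so. What remains is that the limit to unobtained scores is not written, although Analyses does write one.

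Four other stronger readings also go too far:

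- **That the label fits no defined outcome.** Alcohol relapse is defined under Secondary outcome measures; the mismatch there is in the trigger. For anxiety, the abstract mentions blinded diagnostic status and Table 1 schedules the ADIS-IV at three months, so a categorical status is collected. Neither outcome section lists an anxiety relapse, however.
- **That unblinded treating staff would assign the label.** The section names nobody, so this is conjecture.
- **That the combined arm will deteriorate more.** The Background describes an earlier trial with more drinking under combined treatment. It does not report more referrals, and that treatment was not integrated.
- **That counting referral as a bad outcome is an error.** It is a recognised composite approach, so the choice is one of estimand.

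A further fair point is that residential care may suppress drinking, so an observed TLFB score can look better than the participant's condition. Carrying forward a month of abstinence does not solve that.

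The open choice between the two estimation methods also appears in Analyses and may be settled in an analysis plan not shown. It is not a finding here.

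**Conclusion.** The point holds in limited form. Safety net does not restrict estimation to assessments that were not obtained, which is inconsistent with Analyses and with the follow-up provisions. Followed as written with carry-forward, it would normally assign a pre-deterioration score to someone labelled relapsed. The anxiety label corresponds to no listed primary or secondary outcome, and the alcohol label has a different trigger from the listed relapse outcome.

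The size is uncertain and may be small. With a 1 SD gap it runs from zero at equal rates, through 0.01 SD, to 0.10 SD at 15% versus 5%. It favours whichever arm has more deterioration, provided that the estimated scores are better than the true ones. These figures rest on assumed rates and an assumed gap, and they apply only if estimated scores are in fact used for referred participants. The documents do not establish that the results will be biased or which arm would benefit. They do show a rule that permits the bias and is easily tightened.

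**What to change.** Reword the outcome-data sentences in Safety net to state that:

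1. Referred participants continue all scheduled blinded assessments, and their observed scores enter the continuous outcome analyses.
2. Estimation is used only where an assessment was not obtained, by multiple imputation or through the random effects model, and not by carrying forward a pre-deterioration value. An imputation model should include the referral as a predictor.
3. Time to relapse keeps its TLFB definition. The anxiety relapse label is dropped or tied to a defined outcome.
4. Referral for deterioration is reported by arm as a separate outcome. If the sponsor wants it to count as an unfavourable event, that is done in a sensitivity analysis.

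The cost is protocol wording. Some assessments may have to be done by phone or home visit, which Participant retention already allows; no visits are added. One small downside is that drinking observed during residential care may look favourable. Reporting referrals by arm makes that visible.
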